#### ***Process evaluation***

To determine the effectiveness of the TRANSLATE elements, it is crucial to first determine the degree of adoption by the practice, and then systematically document the challenges and enablers of the implementation process, including the role of facilitation and the contextual factors that contribute to success. Qualitative measures will be collected in tandem with the implementation of facilitated TRANSLATE elements to support real-time learning and a reiterative process of evaluation (Table 3).

**Table 3 T3:** Process evaluation activities

**Process evaluation activities**	**When collected**	**Arm(s)**
• Survey of practices' approaches to chronic care and practice change	Baseline Endpoint	Facilitated-CDS and CDS-only
• Semi-structured interviews with each Physician/ Clinician Champion.	Baseline Endpoint	Facilitated-CDS and CDS-only
o Interviews conducted with ALL Facilitated practices		
o Interviews conducted with 9 CDS-only practices (4–5 from each round)		
• Facilitator activity log on all interactions with the practice including:	Ongoing	Facilitated- CDS
o Emails		
o Phone calls		
o Monthly meetings with site coordinator		
o QI team meetings		
o Webinars/Conference calls		
o Collaborative learning		
o Interface/Meetings/consultations with the academic mentors		
• Academic detailing activity log on interactions with the practice including:	Weekly debrief with	Facilitated- CDS
o Phone calls with physicians	each academic mentor	
o Emailsntd	on their contacts with	
o Webinars/Conference calls	the practices	
o Collaborative learning		
o Interface/Meetings/consultations		
• Site visits to 10 interventions and 10 comparator practices to observe workflow.	Final 18 months of	Facilitated-CDS and CDS-only
o Comparator practices selected at random.	intervention	
o Intervention practices selected using a dynamic multi-method approach (refer to		
o site visit protocol)		

Semi-structured interviews will be conducted with the physician champions at baseline and endpoint, asking about their care of patients with CKD and workflow processes in their office. Members of the evaluation team will also conduct site visits at endpoint with both intervention and comparator practices.

E-mail and other communication between practice facilitators and the sites will be analyzed by the evaluation team. Facilitators will also collect notes of meetings, and practice activities; and submit this information to the evaluation team on a regular basis.

#### ***Cost-effectiveness analysis***

The hypothesis is that the intervention of CDS plus the facilitated-TRANSLATE is more cost-effective than the intervention of CDS alone, so the economic analysis will focus on the TRANSLATE elements in delaying CKD progression and reducing mortality due to CKD in the practice settings of primary care physicians. Because there is not a true control group (no clinic practice has no intervention), the proposed project will examine the relative costs of these interventions.

Three types of costs will be included into the total costs of each intervention: the cost of providing services in the clinic practices; the cost of treating CKD; and the other healthcare expenses for patients. We plan to survey a sample of randomly selected practice clinics to measure the cost of providing CKD services. The investigators have created and used a spreadsheet and guideline for collecting cost data from practices for previous studies [39,40]. The practice facilitation activities of TRANSLATE are expected to lead to more costs in the intervention practices. The cost of training clinic practices to use the CDS system and functions of TRANSLATE will also be included into this type of cost, and the cost of training (time) will be measured based on the hourly wages of physician or medical staff. The cost of treating CKD and other healthcare costs for patients will be based on the claims data that we acquire from DARTNet.

### Data analysis

#### ***Clinical data***

The effectiveness measures will include the degree of evidence-based guideline-concordant care for CKD patients (a patient-level score based on the percentage of goals achieved); CKD progression for patients with stage three and four CKD; and all-cause mortality rate.

#### ***Data analysis for hypothesis 1.1 (degree of evidence-based care)***

The primary outcome for this analysis will be a patient-level score based on the percentage of goals achieved. Each goal will be assessed using EHR data for the previous year (or part of the year in which the patient is eligible) at baseline, 12 months, 24 months, and 36 months. Secondary analyses will examine each outcome individually using all available data and continuous measures (*e.g.*, SBP, HbA1c, LDL) or dichotomous measures (ACE/ARB, referral, smoking, NSAIDS). The structure of the data is hierarchical (patients nested within practices) and longitudinal (repeated assessments on patients at baseline, 12, 24, and 36 months).

#### ***Data analysis for hypothesis 2.1 (CKD progression)***

The outcome for this analysis will be eGFR measurements over time. There will be multiple eGFR measures per patient over the duration of the study. We will use general linear mixed-effects models to estimate the rate of decline in eGFR (random intercept, random slope) and the degree to which the baseline covariates predict eGFR. Time for each observation will be coded as days since baseline, converted to months to aid interpretability. The primary hypothesis of difference in slope between treatment groups, adjusting for socio-demographic and clinical covariates, will be tested.

#### ***Data analysis for hypothesis 2.2 (all-cause mortality)***

All-cause mortality will be confirmed using the National Death Index to determine the exact date of death. The outcome for the analysis will be time from baseline to death. Patients who are alive at the end of the study period will be censored at the end of the follow-up time. Assumptions of the proportional hazards model will be checked for each variable. Covariates will include baseline eGFR, defined as the mean of the last two eGFRs prior to study entry, as well as socio-demographic and clinical characteristics.

#### ***Process evaluation***

Qualitative data for the process evaluation will be analyzed using an immersion-crystallization approach [41,42]. This content-driven approach allows the data to speak for itself, as researchers immerse themselves in the data repeatedly to identify themes that emerge [41]. Themes are identified around concepts that are expressed repeatedly in the text and constantly compared back to the data to ensure that they represent the data accurately. Once themes are identified using this method, an additional step in the analysis will be to compare the themes with the elements of the TRANSLATE model to determine how well the data complement the interventional model and how the data can illuminate the process of practice adoption of each element.

#### ***Cost-effectiveness analysis***

Analysis will compare the effectiveness-cost ratios between the two arms to examine which intervention is more cost-effective. Because of the available claims data, electronic medical records data, and mortality data from the National Death Index, the analysis will calculate the quality-adjusted life years (QALYs) lost due to CKD for both interventions. The QALYs will be the most important effectiveness measure in the economic analysis, because QALYs can be valued as a dollar amount. In the United States, $50,000 per QALY is a decision rule that is often used to guide interpretation of cost-effectiveness analyses. We will also do sensitivity analysis by replacing this decision rule with $25,000 or $100,000. We will compare the effectiveness (dollar values of QALYs) with the cost, and determine whether the effectiveness is larger than the cost for each intervention. If the effectiveness is larger than the cost, these interventions will have cost savings. If both interventions will produce cost savings, the proposed project will compare the cost savings for these two interventions and determine which intervention has a high cost saving amount.

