#### ***Hypothesis 3.1***

The intervention of CDS plus TRANSLATE is more cost-effective than the intervention of CDS alone.

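### The economic analysis for aim 3 states two between-arm rules that can disagree, applies one of them only conditionally, and leaves the sign of the QALY measure undefined

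*Protocol article*

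**What the plan says.** Hypothesis 3.1 is a comparison of the two randomised arms: "The intervention of CDS plus TRANSLATE is more cost-effective than the intervention of CDS alone".

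The cost-effectiveness paragraph under Data analysis in the protocol article then sets out, in this order:

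- a ratio comparison: "Analysis will compare the effectiveness-cost ratios between the two arms to examine which intervention is more cost-effective";
- the quantity to be computed: "the analysis will calculate the quality-adjusted life years (QALYs) lost due to CKD for both interventions";
- the role of that quantity: "The QALYs will be the most important effectiveness measure in the economic analysis, because QALYs can be valued as a dollar amount";
- a base-case value of $50,000 per QALY, with $25,000 and $100,000 as sensitivity values;
- a verdict for each arm separately: "We will compare the effectiveness (dollar values of QALYs) with the cost, and determine whether the effectiveness is larger than the cost for each intervention";
- a label for a positive result: "If the effectiveness is larger than the cost, these interventions will have cost savings";
- a second between-arm comparison, with a condition attached: "If both interventions will produce cost savings, the proposed project will compare the cost savings for these two interventions".

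The cost-effectiveness paragraph under Data collection adds two relevant facts. It expects facilitation to raise costs in the intervention practices. It also says "Because there is not a true control group (no clinic practice has no intervention" and accordingly limits the work to relative costs.

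**The concern.** The section opens with one way of ranking the arms and closes with another, and gives no order of precedence. An average ratio for each arm does not answer whether the extra QALYs from facilitation are worth the extra money, which is what a value per QALY is for. The likely case here, more cost and (if the intervention works) more QALYs, is the one in which average ratios and the incremental comparison can part company.

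Three further features make the rule unsafe to apply as written:

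- The net-amount comparison is stated only for when both arms are positive.
- The verdict for each arm has no reference to be measured against.
- QALYs lost are a harm, yet nothing says how they become a measure of effectiveness.

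At stake is the conclusion for one of the trial's three specific aims. The analyst could report either arm as preferred, depending on which sentence is followed, or could report cost savings where spending has risen.

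**Working it through.** The article gives no cost or QALY figures and no computed economic result, so there is nothing to reproduce. All per-patient means below are assumed for illustration. Only the values of a QALY, λ = $25,000, $50,000 and $100,000, come from the article. A is CDS alone, B is CDS plus TRANSLATE, E is QALYs, C is cost, and Δ is B minus A.

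**1. The two rules on the same figures.** Assume A: $1,000, 0.10 QALY; B: $2,500, 0.15 QALY.

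- Average cost per QALY: A 1,000/0.10 = $10,000; B 2,500/0.15 = $16,667. The ratio rule picks A.
- ICER = ΔC/ΔE = 1,500/0.05 = $30,000 per QALY.
- Net amount by arm = λE − C:

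| λ | A | B | B − A |
|---|---|---|---|
| $25,000 | $1,500 | $1,250 | −$250 |
| $50,000 | $4,000 | $5,000 | +$1,000 |
| $100,000 | $9,000 | $12,500 | +$3,500 |

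The last column equals λΔE − ΔC, the incremental net monetary benefit. It picks B at $50,000 and $100,000, and A at $25,000. The ratio rule picks A whatever λ is.

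**2. Why they differ.** With ΔE > 0 and ΔC > 0, E_B/C_B > E_A/C_A is equivalent to ΔC/ΔE < C_A/E_A. So the ratio rule replaces λ by arm A's own average cost per QALY. Here that is $10,000, and $30,000 exceeds it.

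The disagreement also appears at the scale of total costs. Assume A: $30,000, 2.00 QALYs; B: $31,000, 2.05 QALYs. QALYs per $100,000 are 6.667 and 6.613, so the ratio rule picks A. The ICER is 1,000/0.05 = $20,000, and the incremental net monetary benefit is +$250, +$1,500 and +$4,000 at the three thresholds, so B is preferred at every one.

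**3. The both-positive condition.** Assume A: $80,000, 2.00 QALYs; B: $83,000, 2.05 QALYs. At λ = $25,000 the net amounts are 50,000 − 80,000 = −$30,000 and 51,250 − 83,000 = −$31,750. The stated comparison does not apply, although the difference, −$1,750, plainly ranks the arms.

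**4. The sign of QALYs lost.** Assume losses of 0.50 (A) and 0.45 (B), with costs of $30,000 and $31,000.

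| λ | B − A, losses entered as a benefit | B − A, losses entered as a loss |
|---|---|---|
| $25,000 | −$2,250 | +$250 |
| $50,000 | −$3,500 | +$1,500 |
| $100,000 | −$6,000 | +$4,000 |

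The ranking reverses at all three values. With the proper sign, each arm's net amount is −λ × loss − cost. At $50,000 that is −25,000 − 30,000 = −$55,000 for A and −22,500 − 31,000 = −$53,500 for B. This is negative for any positive loss and cost, so the both-positive condition would never be met.

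**5. The missing reference.** Return to $30,000 and 2.00 QALYs against $31,000 and 2.05 QALYs at λ = $50,000, and subtract an assumed untreated reference from both arms.

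| Reference | A | B | B − A |
|---|---|---|---|
| 1.9 QALYs, $29,000 | $4,000 | $5,500 | $1,500 |
| 1.5 QALYs, $20,000 | $15,000 | $16,500 | $1,500 |
| 0 QALYs, $0 | $70,000 | $71,500 | $1,500 |

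The result for each arm depends entirely on the unobserved reference. The difference between arms does not.

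**The case against.** The strongest reply is that the section's last step already does the right thing. On the figures in step 1, comparing the two net amounts gives exactly the incremental net monetary benefit, and both arms are positive at every threshold, so the plan's condition is met. That is correct. The example shows two stated rules in conflict; it does not show the plan's threshold rule reaching a wrong answer.

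A reader might infer from the missing control group that hypothesis 3.1 cannot be tested. The documents do not support this. The hypothesis compares the two randomised arms, any untreated reference cancels (step 5), and the article itself confines the work to relative costs. Only the intermediate verdict for each arm lacks a reference.

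A reader might also infer that the plan rewards the arm losing more QALYs. That is the literal reading of an ambiguous text and should not be stated as the plan's intention. The decision sentence speaks of QALYs without the word lost, and the Data collection paragraph places the benefit in slower progression and lower mortality. What stands is that QALYs lost are the only QALY quantity defined and no conversion is given.

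Calling a net benefit a cost saving can be defended as terminology, since the article defines it on the spot and the ranking is unaffected. It still misleads: in step 1 arm B shows $5,000 of savings at $50,000 while costing $1,500 more than A. Finally, methods for uncertainty are properly left to a fuller plan, and their absence here is no defect.

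**Conclusion.** The point holds as a fault in the stated decision rule for aim 3, not in the design or the data. The opening ratio comparison ignores the plan's own thresholds and can favour the wrong arm. The closing net-amount comparison can contradict it, is silent when both arms are negative, and is mislabelled as cost savings. The QALY measure has no stated sign, and a literal reading would reverse the ranking.

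In the worked case the two rules pick different arms at $50,000 and $100,000 and agree at $25,000. The size rests wholly on assumed costs and QALYs, so how often the rules would disagree in this trial is unknown. That they can disagree follows from the algebra in step 2 and needs only that facilitation adds both cost, which the article expects, and QALYs.

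**What to change.** In the cost-effectiveness paragraph under Data analysis:

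- Remove the comparison of effectiveness-cost ratios by arm, the separate verdict for each arm, and the condition that both arms be positive.
- State one decision rule: the incremental net monetary benefit of CDS plus TRANSLATE against CDS alone, λ × (difference in mean QALYs) − (difference in mean cost), at $50,000, with $25,000 and $100,000 as sensitivity values.
- Define the QALY difference so that losses averted count as gains.
- Report the ICER alongside, with uncertainty that respects the randomised clusters, for example a bootstrap that resamples them.
- Use the term cost saving only when the cost difference is negative.

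The cost is a rewording; the data to be collected are the same. The Trial status section says data analysis has not yet occurred, so the rule can be settled before results are seen.

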#### ***Hypothesis 2.3***

The process evaluation will determine through qualitative methods the fidelity of the facilitated TRANSLATE program; find the challenges and enablers of the implementation process, and the contextual factors that contribute to TRANSLATE decisions and strategies; and translate lessons learned into pragmatic ‘best practices’ for future facilitation and dissemination.

### Specific Aim 3

Conduct a cost-effectiveness analysis that will compare the benefit of the intervention of CDS alone against the intervention of CDS plus TRANSLATE (practice facilitation) in relationship to overall cost per quality adjusted years of life.

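### The economic analysis counts QALYs and deaths attributed to CKD, but the aim, the mortality outcome and the costs carry no such restriction

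*Protocol article*

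**What the plan says.** **Aim.** Specific Aim 3 compares the two interventions "in relationship to overall cost per quality adjusted years of life". The abstract puts it the same way. Neither limits QALYs to a cause.

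**Effect in the economic sections.** Under Data collection, Cost-effectiveness analysis, the focus is on the TRANSLATE elements in "delaying CKD progression and reducing mortality due to CKD in the practice settings of primary care physicians". Under Data analysis, Cost-effectiveness analysis, "the analysis will calculate the quality-adjusted life years (QALYs) lost due to CKD for both interventions". The same paragraph adds: "The QALYs will be the most important effectiveness measure in the economic analysis". Their dollar value is then compared with cost, using $50,000 per QALY, with $25,000 and $100,000 as sensitivity values.

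**Costs.** Besides the cost of providing services in the practices, the plan counts "the cost of treating CKD; and the other healthcare expenses for patients". On their source: "The cost of treating CKD and other healthcare costs for patients will be based on the claims data".

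**Mortality in the trial.** Hypothesis 2.2 and its analysis concern death from any cause: "All-cause mortality will be confirmed using the National Death Index to determine the exact date of death".

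**The concern.** A cost-effectiveness ratio needs a numerator and a denominator of the same scope. Here the cost covers all healthcare, while the effect, as worded, covers only what is attributed to CKD. A patient who lives longer because of better blood pressure control or stopping smoking (both among the seven audited measures in Table 1) goes on generating healthcare costs, which are counted. The life-years gained count only so far as they are assigned to CKD.

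Two things are at stake. An analyst who follows the words literally would compute something other than what Aim 3 asks for. That analyst would also have to split deaths and quality-of-life losses into CKD and non-CKD parts, and the article states no method for the split.

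**Working it through.** The article gives no QALY gain, incremental cost or economic result, so there is no figure to reproduce. The check is a comparison of text, followed by the algebra of the mismatch.

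**Step 1. Scope of each component**

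| Component | Place in the article | Restricted to CKD? |
|---|---|---|
| QALYs in the aim | Specific Aim 3; abstract | No |
| Mortality outcome | Hypothesis 2.2 and its data analysis; list of effectiveness measures | No, all-cause |
| Costs | Data collection, Cost-effectiveness analysis | No, CKD treatment and other healthcare |
| Mortality benefit in the economic focus | Data collection, Cost-effectiveness analysis | Yes |
| QALYs in the economic analysis | Data analysis, Cost-effectiveness analysis | Yes |

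The restriction appears in two separate sections, both on the effect side and neither on the cost side.

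**Step 2. Basis for attribution**

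The Clinical data section ascertains death from practice records or death-registry linkage. The analysis for Hypothesis 2.2 uses the National Death Index for the date of death. Table 2 lists diagnoses but no cause of death. No section states how a death or a QALY loss is to be assigned to CKD.

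**Step 3. Effect of the mismatch**

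Let ΔC be the difference between arms in total cost per patient, ΔQ the difference in all-cause QALYs, s the share of ΔQ attributed to CKD, and λ the dollar value of a QALY.

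- Matched scope: cost per QALY = ΔC/ΔQ; difference in net benefit = λΔQ − ΔC.
- As literally worded: cost per QALY = ΔC/(sΔQ); difference in net benefit = λsΔQ − ΔC.
- Ratio of the two costs per QALY: [ΔC/(sΔQ)] / [ΔC/ΔQ] = 1/s.
- Net benefit is understated by λ(1 − s)ΔQ.

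The plan values QALYs in dollars for each arm and, where both arms show savings, compares the savings. The difference between arms in that quantity is the net-benefit expression above, so the algebra carries over to that comparison.

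The multiplier depends only on s: 1/0.75 = 1.33, 1/0.5 = 2, 1/0.25 = 4.

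**Step 4. Illustration with assumed inputs**

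Neither value is in the article. Assume ΔQ = 0.03 and ΔC = $1,000 per patient.

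| s | Cost per QALY | Net benefit at $25,000 | at $50,000 | at $100,000 |
|---|---|---|---|---|
| 1 | 1,000/0.03 = $33,333 | −$250 | +$500 | +$2,000 |
| 0.75 | 1,000/0.0225 = $44,444 | −$438 | +$125 | +$1,250 |
| 0.5 | 1,000/0.015 = $66,667 | −$625 | −$250 | +$500 |
| 0.25 | 1,000/0.0075 = $133,333 | −$812 | −$625 | −$250 |

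Under these assumptions the sign at $50,000 changes when s falls below 1,000/(50,000 × 0.03) = 0.667, and at $100,000 below 1,000/(100,000 × 0.03) = 0.333. At $25,000 it is negative throughout. Other inputs would move these points; the 1/s relation would not change.

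**The case against.** The best defence is that the wording is loose. Every analysed patient has stage three or four CKD, so QALYs lost due to CKD may simply mean QALYs lost in this population. The trial's only mortality outcome is all-cause, no attribution step is described, and the Limitations expect to collect quality-of-life measures, which suits ordinary QALYs. The word overall in Aim 3 qualifies cost, not QALYs. The article is also condensed, and construction of QALYs is commonly left to a fuller document. All of this is fair, and the intended analysis may well be all-cause. What remains is that the article does not merely omit a detail. It states a main effectiveness measure that differs in scope from its aim and its costs, and does so in two sections.

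Three stronger readings are tempting but not supported.

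- **That deaths cannot be attributed to CKD from the planned data.** The article names the date of death as the purpose of the index for Hypothesis 2.2, but the economic section cites mortality data from the same index without that limit. All that can be said is that no rule or cause-of-death variable is stated.
- **That most of the benefit must be non-renal, from the five-year figures in the Background.** For stage three these are 24.3% deaths against 1.3% renal replacement (24.3/1.3 = 18.7). Renal replacement is not CKD death, and neither figure measures deaths the intervention could prevent. Stage four, also in the trial, gives 45.7% against 19.9% (45.7/19.9 = 2.3). Neither ratio estimates s.
- **That the plan's thresholds would be crossed.** This depends entirely on an assumed gain, cost and share.

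**Conclusion.** The point holds as an inconsistency of scope. Aim 3, the mortality outcome and the costs are unrestricted by cause; the main economic effect, as worded, is restricted to CKD.

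The consequence is conditional. It needs the literal reading to be followed, 0 < s < 1, and a positive gain outside CKD. Cost per QALY is then inflated by 1/s, for example twofold at s = 0.5, and dollar-valued benefit is understated by λ(1 − s)ΔQ. If the effect outside CKD were negative while the total gain stayed positive, s would exceed 1 and the distortion would run the other way. The article does not give s, so the size is unknown.

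A reader might infer that the economic comparison is biased against the facilitated arm. The article does not establish that: it shows neither that the restricted measure would be computed nor that the facilitated arm has a gain outside CKD. The matter concerns the third aim and leaves the clinical outcomes untouched, but it should be settled before the economic data are analysed.

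**What to change.** In both Cost-effectiveness analysis sections, replace the CKD-attributed QALYs and CKD-attributed mortality with total QALYs per patient, built from all-cause survival (the Hypothesis 2.2 outcome) and weighted by quality of life. State the same measure in the abstract and Specific Aim 3, and pair it with the all-healthcare costs already planned. Expressing the effect as QALYs accrued also makes its direction clear, since fewer QALYs lost is the better result.

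If a CKD-only result is wanted, make it secondary, state the attribution rule, and set it against CKD-only costs.

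The cost is mainly wording. Death dates and claims are already planned, and the article reports that no data analysis had yet occurred. The change does not by itself secure the data. The Limitations warn that Medicare claims may be available only for a sample and quality of life only for a subsample, so the revised text should say in which patients costs and total QALYs will be measured.
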